## Abstract

**Background:**

Recent scientific evidence has challenged the traditional “rest-is-best” approach for concussion management. It is now thought that “exercise-is-medicine” for concussion, owing to dozens of studies which demonstrate that sub-maximal, graded aerobic exercise can reduce symptom burden and time to symptom resolution. However, the primary *neuropathology* of concussion is altered functional brain activity. To date, no studies have examined the effects of sub-maximal aerobic exercise on resting state functional brain activity in pediatric concussion. In addition, although exercise is now more widely prescribed following concussion, its cardiopulmonary response is not yet well understood in this population. Our study has two main goals. The first is to understand whether there are exercise-induced resting state functional brain activity differences in children with concussion vs. healthy controls. The second is to profile the physiological response to exercise and understand whether it differs between groups.

**Methods:**

We will perform a single-center, controlled, prospective cohort study of pediatric concussion at a large, urban children’s hospital and academic center. Children with sport-related concussion (aged 12–17 years) will be recruited within 4-weeks of injury by our clinical study team members. Key inclusion criteria include: medical clearance to exercise, no prior concussion or neurological history, and no implants that would preclude MRI. Age- and sex-matched healthy controls will be required to meet the same inclusion criteria and will be recruited through the community. The study will be performed over two visits separated by 24–48 h. Visit 1 involves exercise testing (following the current clinical standard for concussion) and breath-by-breath gas collection using a metabolic cart. Visit 2 involves two functional MRI (fMRI) scans interspersed by 10-minutes of treadmill walking at an intensity calibrated to Visit 1 findings. To address sub-objectives, all participants will be asked to self-report symptoms daily and wear a waist-worn tri-axial accelerometer for 28-days after Visit 2.

**Discussion:**

Our study will advance the growing exercise-concussion field by helping us understand whether exercise impacts outcomes beyond symptoms in pediatric concussion. We will also be able to profile the cardiopulmonary response to exercise, which may allow for further understanding (and eventual optimization) of exercise in concussion management.

**Trial registration:**

Not applicable.

**Supplementary Information:**

The online version contains supplementary material available at 10.1186/s13102-024-00926-1.

## Introduction

Concussions are a form of traumatic brain injury (TBI) that pose considerable healthcare burden [1, 2]. Recent incidence estimates, based on physician billing data from Ontario, Canada, suggest an annual incidence of 1,153/100,000 residents [3]. This injury impacts individuals throughout the lifespan, though the incidence of concussion is amongst the highest in pediatric populations [3, 4], a group in which symptoms often also take longer to resolve [5, 6]. In pediatric concussion, greater symptom severity is a predictor of protracted recovery (taking 30-days or longer) [6, 7], and the injury is also often co-morbid with poorer mental health [8] and quality of life [9–11]. Despite all this, treatment options for concussion have historically remained limited [12–14].

Until recently, concussion management was governed by a “rest-is-best” approach, which is now being supplanted by an “exercise-is-medicine” mindset [15]. More specifically, graded, sub-maximal aerobic exercise (performed on a stationary bike or treadmill) is becoming part of best clinical practice [16], with dozens of studies now supporting the use of exercise to reduce concussion symptoms and/or time to recovery. A recent meta-analysis of 23 studies showed that sub-maximal aerobic exercise had a large effect (*Hedge’s g* = 1.71) on concussion recovery, operationalized as a reduction in concussion symptoms [17]. Adding to this, another recent systematic review and meta-analysis of randomized controlled trials in the field (*n* = 7; *N* = 326) reached a similar conclusion, finding that sub-maximal aerobic exercise significantly improved symptoms (standard mean difference [SMD]: -0.44 [-0.68, -0.19]) [18]. There is a substantial and growing evidence base that supports the use of sub-maximal aerobic exercise as a treatment option for concussion symptoms. Yet the field recognizes that symptom recovery does not equate to physiological recovery from concussion [19].

Concussions, by definition, are not associated with structural injury; rather, their primary neuropathology is functional neurological disturbance [16]. As such, numerous studies have reported that there are functional neuropathological disturbances (typically observed using resting-state functional MRI; rsfMRI) in pediatric concussion [20–25]. Recently, the largest neuroimaging cohort of pediatric concussion reported that in comparison to children with orthopedic injury (who served as an injury-control group), children with concussion had regional and global network abnormalities in the rsfMRI signal (as computed using graph theory metrics including degree centrality, efficiency, and clustering coefficient), which persisted in some cases up to 6-months post-injury [26]. Functional neurological disturbance is commonplace in concussion, even in those who are asymptomatic [19]. To date, no studies have examined the effects of exercise on functional brain activity in pediatric concussion. Analogous studies, however, have been performed in adults. More specifically, two studies (on one cohort of adults with mild TBI) found that an aerobic exercise stimulus (similar to that being currently prescribed for concussion management) led to hypo-connectivity between several brain regions, including those that comprise the default mode network [27, 28]. Similar data are unavailable in pediatric concussion, leaving a gap in our understanding of how exercise impacts the concussed pediatric brain. Whether such functional neurological disturbance translates to sport-specific consequences, such as gait abnormalities as measured by accelerometers, also requires further study in pediatric concussion. Further, despite increased interest in prescribing exercise as a treatment for concussion, the role of exercise testing as a diagnostic or prognostic tool has remained relatively understudied, leaving another important knowledge gap. To date, two studies have collected exercise physiology data while children with concussion performed sub-maximal aerobic exercise [29, 30]. The first of these reported no groupwise differences (i.e., concussion vs. healthy) in resting heart rate, systolic and diastolic blood pressure, or changes in V̇O_2_, V̇CO_2_, or minute ventilation from baseline to test termination; only ratings of perceived exertion significantly differed (29). Similarly, the second study reported no groupwise differences in the outcomes they collected, namely: heart rate change throughout the test, blood pressure responses to exercise, or differences in end-tidal O_2_ or CO_2_ [30]. Additional research is required to add to these findings and provide initial insights into how sub-maximal metrics (such as the oxygen uptake efficiency slope; OUES [31] respond to exercise in pediatric concussion. Further, while there are data on gait and balance in concussion [32, 33], studies have not yet examined gait differences between children with concussion and healthy controls during a controlled, progressive sub-maximal aerobic exercise session. Such accelerometer data, combined with exercise physiology data, may offer additional insight into how gait varies as a function of exercise intensity of perceived exertion, which can have implications for return-to-sport.

To address these knowledge gaps, we performed a prospective, single-center controlled cohort study involving children with a sport-related concussion (aged 12–17) and age- and sex-matched healthy peers. The primary objective of our study was to understand the effects of a single bout of aerobic exercise (modelled on the current standard for exercise testing in concussion [16]) on rsfMRI network connectivity. We hypothesized, based on analogous data in adults, that exercise would lead to generalized patterns of hypo-connectivity in those with a concussion. Our second objective was to use breath-by-breath exercise physiology (collected during a progressive, sub-maximal aerobic treadmill test) to understand cardiorespiratory response to graded aerobic exercise in this population. Per prior research, we hypothesized that children with concussion would perceive exercise to be more difficult in comparison to their peers. Further, given the known autonomic dysfunction that occurs in concussion [34], we hypothesized that there would be an attenuated cardiopulmonary response to exercise in children with concussion in comparison to healthy controls. A third objective was to understand if there were gait abnormalities in children with concussion (measured using a tri-axial, waist-worn accelerometer) over the duration of a controlled, graded treadmill test. We hypothesized that there would be more variability in the anterior-posterior and medio-lateral planes in children with concussion vs. healthy peers, and that this variation would increase with exercise intensity.

## Methods

### Design

This proposed study is a single-center, prospective cohort study, with fMRI scans immediately before and after a single bout of aerobic exercise. Gait will also be assessed during this bout of exercise using a waist-worn, tri-axial accelerometer. This study will also include a 28-day follow-up period (to monitor daily symptoms and habitual physical activity) beginning after the MRI, as well a healthy control group matched for sex, biological age (to control for the potential confounding effects of maturational status) and sport participation.

### Study participants

*Patients*: *Inclusion criteria*: **1**) Emergency department or urgent care clinic diagnosis of concussion, made by a physician with experience in pediatric brain injury and/or sports medicine in accordance with the diagnostic criteria from recent consensus statements on concussion in sport [16, 35]. **2**) Participants must be within four-weeks of injury at the time of recruitment. **3**) Age of 12 to 17 years. Our group has found that children younger than 12 have difficulty laying still during the MRI, resulting in motion artifacts that may limit data quality. The age limit for pediatric clinics at our children’s hospital is 17. While there are neurodevelopmental changes occurring throughout this age group, children of this age range are expected to be in a similar neurodevelopmental window; biological age will nonetheless be used as a moderator variable in analyses. **4**) Medical clearance (per the emergency department physician) to perform aerobic exercise test on a treadmill. **5**) Fluency in English to provide informed assent and consent (for parents) and ensure symptom report validity (as measures are validated in English). *Exclusion criteria*: **1**) Previous history of suspected concussion or other neurological comorbidity (as per self-report) that may confound neuroimaging findings. **2**) Complicated mild or moderate-to-severe brain injuries. **3**) Mobility, gait, or vestibular impairments that preclude safe exercise. **4**) Claustrophobia or post-surgical metallic inclusions (e.g., pacemaker, neurostimulators, aneurism clips) that may prevent safe MRI testing.

*Healthy controls*: *Inclusion criteria*: **1**) Age of 12 to 17 years. **2**) Fluency in English to provide informed consent and ensure symptom report validity. *Exclusion criteria*: **1**) Present or previous history of concussion or other neurological comorbidity (as per self-report). **2**) Mobility, gait, or vestibular impairments that preclude safe exercise. **3**) Claustrophobia or metal implants/devices that are contraindicated for MRI testing.

### Recruitment strategy

#### Patients

Children with concussion will be recruited from the McMaster Children’s Hospital Emergency Department and an associated Urgent Care Clinic. We selected these centers as our recruitment sites because: **1**) they have a large catchment area, with an annual throughput of approximately 250 children with concussion (or 5 patients per week) within the age range of interest, **2**) it permits recruitment while participants are in the acute stages of concussion, **3**) our already strong and positive relationship with emergency medicine physicians (who are experienced in pediatric concussion) will facilitate recruitment, **4**) they are based in a metropolitan area with a population of ~ 750,000, and our sample is thus estimated to draw from a representative population which precludes the need for stratified sampling.

#### Healthy controls

Healthy controls will be recruited through advertisement in community settings (e.g., local sports facilities, youth clubs) and through our existing networks, including mailing lists of individuals who agreed to be contacted about participation in future research studies.

### Study protocol

Data will be collected over 30-days, including 2 study visits (separated by 24-48-hours to ensure physiological recovery following exercise) and a 28-day follow-up period for symptom monitoring. The purpose of Visit 1 is to assess exercise tolerance of each participant so that the intensity of the exercise test to be performed on Visit 2 can be calibrated to individual capacity. The purpose of Visit 2 is to assess the effects of exercise on resting state functional brain networks.

#### Visit 1

The first study visit will take place in the exercise laboratory of the Child Health and Exercise Medicine Program at McMaster Children’s Hospital. Participants and their parents will first complete assent and consent forms, as well as demographic and medical intake questionnaires. Participants will then perform a baseline exercise test of aerobic fitness (the Buffalo Concussion Treadmill Test; BCTT), detailed below.

#### Visit 2

The second study visit will occur at the Imaging Research Centre at St. Joseph’s Healthcare, Hamilton. Here, participants will first complete a baseline MRI (as per the imaging parameters in the *Measurements* section). Participants will then exercise on a treadmill adjacent to the MRI room for 10 min at an intensity equivalent to 85% of the maximum intensity achieved during the exercise test performed at Visit 1. Participants will then re-enter the MRI (which can be done in under 150 s, as per our pilot data) for post-exercise scanning using the same fMRI protocol. Physiological metrics will be continuously monitored and recorded throughout imaging using MRI compatible pulse oximeter. Based on our pilot data (including 5 children with concussion and 4 healthy controls), we have not encountered any difficulties with the MRI (with respect to excessive motion or in-and-out times) and all participants tolerated the duration of our imaging protocol. Each participant will be given a waist-worn accelerometer to measure habitual physical activity, along with wear instructions for the next 28-days.

#### Follow-up

Participants will continue to wear the accelerometer for 28-days after Visit 2; they will then return the accelerometers to our lab in a pre-paid return envelope. During these 28 days, participants will also self-report concussion symptoms using an online version of the PCSS [36] using a secure survey system (RedCAP) every 24 h.

### Measurements

*Aerobic fitness*: This exercise test will follow the parameters of the BCTT, the current standard for evaluating exercise tolerance in concussion. This progressive test involves an increase in incline of 1%/min and a starting speed of either 3.2 or 3.6 mph. The test is terminated when participants self-report maximum exertion, or report a rating of perceived exertion (RPE) ≥ 17 per the Borg RPE Scale [37]. The BCTT is also terminated if patients report a ≥ 3-point increase in concussion symptoms (relative to baseline) on a 10-point visual scale, which is an abbreviated and adapted version of the PCSS. The test is also terminated if the participant reports any distress or discomfort (irrespective of RPE or symptom score). RPE and symptom scores will be recorded every 2-minutes throughout the test. The BCTT has high test-retest reliability (ICC = 0.79) as well as high sensitivity (99%) and specificity (89%) for identifying and ruling out concussion symptoms, respectively [38].

While the BCTT has been widely used to assess aerobic capacity (based on heart rate) in concussion, to the best of our knowledge ours will be one of the first studies to measure inspired/expired O_2_ and CO_2_ continuously throughout the BCTT using a calibrated metabolic cart (Vmax29, SensorMedics, Yorba Linda, CA, U.S.A.). This permits the first opportunity for a breath-by-breath gas analysis during the BCTT, and thus objective measurement of typical exercise testing parameters (e.g., ventilatory threshold, oxygen uptake efficiency slope). Participants will continue to exercise until they reach a symptom-limited threshold. Heart rate will be monitored continually throughout the test and during a 2-minute post-exercise recovery period.

*Anatomical and functional MRI*: Imaging will be performed using a GE 3 Tesla MR750 Discovery MRI scanner and 32-channel phased array RF coil (General Electric Health Care, Milwaukee, WI). Anatomical images will be collected using a 3D IR-prepped fast SPGR T1-weighted sequence (TR/TE = 7.5/2.1ms, TI = 450ms, flip angle = 12°, 512 × 512 matrix, 140–160 slices, 24 cm FOV). Resting state fMRI data (axial 2D acquisition, gradient echo EPI, TR/TE = 2000/35ms, flip angle = 90°, 64 × 64 matrix, 31–35 slices, 300 time points (10 min), 24 cm FOV), will be acquired wherein participants will be asked to remain awake, keep their eyes open, and not to think of anything in particular. A B_o_ map will be acquired for resting state scans, using the same geometric prescription. With regards to logistics, subjects the 3D, resting state and B_o_ maps will be acquired prior to exercise. Immediately following exercise (outside of the scanner) resting state, its corresponding B_o_ map and lastly a 3D scan will be acquired. Preprocessing will be performed using CONN 21a [39], which runs on the functionality of SPM12 [40] and MATLAB [41]. Data from each participant will be corrected for B_0_ field inhomogeneities. All functional data will be registered to the participant’s high resolution T1-weighted anatomical scans, then subsequently registered to MNI152 standard space at 2 mm resampling resolution. BOLD images will be high-pass filtered (cut off at 0.01 Hz for low level noise removal), and spatially smoothed with a Gaussian kernel with full width at half maximum (FWHM) of 6 mm (to improve signal-to-noise ratio).

*Concussion symptoms (PCSS)*: The PCSS is a 22-item questionnaire [36], wherein patients rank the severity of their somatic, cognitive, emotional, and sleep-related symptoms. The PCSS has high internal consistency (Crohnbach α = 0.87), moderate-high test-retest reliability (*r* = 0.65), high sensitivity and specificity (0.819 and 0.849, respectively), and high face and content validity [42]. Further, the PCSS has an abbreviated version that has been used to assess changes in symptoms during the BCTT [43, 44].

#### Accelerometry

Waist-worn accelerometers will be used to measure gait in 3-axis during the Visit 1 treadmill test. More specifically, prior to starting the test, participants will be fitted with the accelerometer on their right hip by research staff. The accelerometer tracks the entirety of the treadmill test, beginning from warm-up. The planned accelerometer we will use is the ActiGraph GT3x, a small and light-weight device that measures orthogonal vectors of acceleration along x-, y-, and z-axes, at 100 Hz sampling. Of note, this accelerometer measures physical activity in acquired brain injury with high reproducibility [45]. Participants will also be asked to wear the accelerometer for 4-weeks after Visit 2, allowing us to understand their patterns of habitual physical activity. During this follow-up period, participants also will be asked to record via a log book when the device was put on and taken off (e.g., when waking and sleeping, or taking a shower), in order to account for true wear-time.

Data from the tri-axial accelerometer will first be cleaned to include only data specific to the treadmill test, from warm-up to test termination. Analyses will focus on understanding whether there is more medio-lateral or anterior-posterior gait variation (operationalized, for example, as the coefficient of variation) in gait in the concussion group, compared to healthy controls. The analysis will aim to determine if there is more gait variation as test intensity (which in this case is represented by treadmill gradient) increases. As above, groupwise differences may be assessed using ANCOVAs (Group x Time), controlling for age and sex, or generalized linear models predicting gait variability on the basis of test time (i.e., intensity), age, and sex.

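### Objective 3: the only gait-variation metric offered, a coefficient of variation, is unstable if taken on raw hip acceleration, and the gait models omit belt speed although the test uses two starting speeds

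*Protocol article*

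**What the plan says.** The third hypothesis, in the Introduction, is "more variability in the anterior-posterior and medio-lateral planes in children with concussion vs. healthy peers", with the variation growing as exercise gets harder.

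The gait signal is described under Accelerometry. The device "measures orthogonal vectors of acceleration along x-, y-, and z-axes, at 100 Hz sampling", and "participants will be fitted with the accelerometer on their right hip by research staff". No other source of gait data is described.

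Under Data analyses, objective 3, the outcome is "more medio-lateral or anterior-posterior gait variation (operationalized, for example, as the coefficient of variation"). The recording is trimmed to the treadmill test, and the analysis then asks whether variation grows as "test intensity (which in this case is represented by treadmill gradient) increases". Two model options are given: a group-by-time ANCOVA controlling for age and sex, or a generalized linear model with test time (equated with intensity), age and sex. Belt speed is in neither.

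Under Measurements, the incline rises by 1% per minute from "a starting speed of either 3.2 or 3.6 mph". The article gives no rule for which child starts at which speed and describes no later change of speed.

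**The concern.** Two choices are at issue, and both bear on whether objective 3 measures gait.

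**The metric.** A CV is SD divided by mean. It suits a positive quantity whose mean is well away from zero. A child walking steadily on a treadmill has almost no net side-to-side or front-to-back acceleration. A hip device that senses gravity therefore records a mean on those axes that is largely g × sin(tilt), set by how the device sits and how the child leans. Dividing by that mean brings placement and posture into the outcome. If lean changes with incline, the denominator moves with the factor under test.

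**The intensity term.** At 1% per minute, gradient and time carry the same information. Neither separates two children at the same minute whose belts run at different speeds, and acceleration amplitude can be expected to depend on speed.

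At stake is whether a positive or negative result on the third hypothesis can be read as a statement about gait.

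**Working it through.** The article states no figure for the gait objective, so there is none to reproduce. Its sample size of 36 per group comes from pilot fMRI data and is used below only as a convenient group size.

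**Inputs from the article:** starting speeds 3.2 and 3.6 mph; incline +1% per minute; covariates age and sex; 36 per group.

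**Assumptions (not in the article):** axis SD 0.10 to 0.25 g; tilt or lean 1 to 10 degrees; amplitude proportional to speed to the power 1 or 2; between-child SD of log amplitude 0.15 to 0.35; share of children at 3.6 mph differing between groups by 0 to 40 percentage points.

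**1. CV on raw axis acceleration, gait held fixed.** CV = SD / (g × sin(tilt)).

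| Axis SD | 1° | 2° | 5° | 10° |
|---|---|---|---|---|
| 0.10 g | 5.73 | 2.87 | 1.15 | 0.58 |
| 0.15 g | 8.59 | 4.30 | 1.72 | 0.86 |
| 0.25 g | 14.32 | 7.16 | 2.87 | 1.44 |

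The ratio between 1 and 10 degrees is sin(10°)/sin(1°) = 0.1736/0.01745 = 9.95, whatever the SD. At zero tilt the CV is undefined.

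**2. Effect on the trend with intensity.** Suppose true SD rises 30%, from 0.150 to 0.195 g, while lean grows from 2 to 6 degrees. The CV goes from 0.150/0.0349 = 4.30 to 0.195/0.1045 = 1.87. The hypothesised rise would appear as a fall.

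**3. Effect on the group comparison.** Simulation: 36 per group, 4,000 runs, two-sided t-test at 0.05, axis SD 0.15 g.

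- True SD 25% higher in one group; tilt centred on 0 with SD 5 degrees; between-child log-SD 0.15 / 0.25 / 0.35. Power with the CV is 3.5% / 2.9% / 2.6%. Power with the axis SD is 100% / 95% / 73%.
- No true difference; mean lean 5 versus 7 degrees (SD 1.5); between-child log-SD 0.15. The CV rejects in 96% of runs, the axis SD in 5.6%.

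The first scenario is severe, because tilt straddles zero and the CV is tested untransformed. A log or rank analysis would be less affected by the extreme values.

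**4. Belt speed.** 3.6/3.2 = 1.125, and 1.125² = 1.266, so amplitude would differ by 12.5% to 26.6% at the same gradient.

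- *Added variance.* With half the children at each speed, the log-SD due to speed is 0.5 × ln(1.125) = 0.059 (power 1) or ln(1.125) = 0.118 (power 2). The variances are 0.0035 and 0.0139. Against 0.15² = 0.0225 they add 15% and 62%. Against 0.35² = 0.1225 they add 3% and 11%.
- *Bias.* The spurious group difference is roughly the gap in shares × the amplitude difference. A 20-point gap gives 0.20 × 12.5% = 2.5% to 0.20 × 26.6% = 5.3%. A 40-point gap gives 5.0% to 10.6%.
- *False positives* (simulated, axis SD as metric, log-SD 0.15). Equal shares: 4% to 5%. A 20-point gap: 10% to 17%. A 40-point gap: 23% to 56%.

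**The case against.** The strongest reply is that nothing here is fixed. The CV is introduced as an example, and the text does not say it is taken over raw axis samples. A CV of a per-stride amplitude on each axis, such as peak-to-peak, has a positive mean, fits the wording equally well and escapes the tilt problem. Gravity removal and stride segmentation are details that an article commonly leaves to a fuller plan. This stands. A reader might infer that the plan commits to a CV of raw acceleration, and the document does not support that. What survives is narrower: the CV is the only metric named, the only signal named is three-axis hip acceleration, and the most direct combination of the two fails.

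On speed, a reader might infer that gradient does not represent intensity. That is too strong. Within a child the incline only rises, so gradient does track intensity, and a constant belt speed shifts that child's level without by itself creating the trend. Nor does the document show that speed biases the group contrast. Controls are matched on sex, biological age and sport participation, the models adjust for age and sex, and with equal speed shares the false-positive rate is nominal. What stands is that the stated covariates omit a known, recorded feature of the test, and that the article gives no allocation rule from which balance could be assumed.

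The tilt, lean, SD and speed-share values are all assumed. Nothing in the article shows that hip-device tilt changes with incline.

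**Conclusion.** The point holds in a conditional form.

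- **Metric.** If the CV is computed on raw medio-lateral or anterior-posterior hip acceleration, it is unsuitable. It can change about tenfold between 1 and 10 degrees of tilt with identical gait, at any SD in the assumed range. If it is computed on a positive per-stride amplitude, this objection falls away.
- **Belt speed.** Its absence from both stated models holds as written. Under the assumptions above, omission adds between 3% and 62% to the between-child variance of log amplitude. It biases the group contrast only if the speed mix differs by group; with equal shares there is no bias.

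This is a correction worth making to one of three objectives. It does not touch the primary fMRI analysis or the sample size.

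**What to change.** In Data analyses, objective 3:

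1. Replace the example metric with the SD or root mean square of gravity-removed acceleration on each axis, computed per one-minute stage. A CV of a positive per-stride amplitude on that axis is an acceptable alternative. A CV of stride time would also avoid the tilt problem, but it has no medio-lateral or anterior-posterior direction and so would not answer the stated hypothesis.
2. Add starting belt speed (3.2 or 3.6 mph) as a covariate beside gradient or time, age and sex, in whichever gait model is used. This matters more once the metric is an SD or root mean square, because amplitude itself can be expected to scale with speed.

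The cost is one model degree of freedom and some extra signal processing. The recordings, visits and test procedure stay as they are.

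### The gait-by-gradient trend compares different children at low and high gradients, and the plan names no within-child model to protect the group comparison

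*Protocol article*

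**What the plan says.** The hypothesis at the end of the Introduction is that gait is more variable after concussion and that "this variation would increase with exercise intensity". For this objective, the Data analyses section cleans the accelerometer record to "include only data specific to the treadmill test, from warm-up to test termination" and then seeks to "determine if there is more gait variation as test intensity (which in this case is represented by treadmill gradient) increases". Two models are offered as options: an ANCOVA (Group x Time) controlling for age and sex, or a generalized linear model with test time, age and sex as predictors.

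Under Measurements (Aerobic fitness), the treadmill test involves "an increase in incline of 1%/min". On stopping it says: "The test is terminated when participants self-report maximum exertion", or report an RPE of 17 or more. Distress or discomfort also ends it. For patients there is a further criterion: "The BCTT is also terminated if patients report a ≥ 3-point increase in concussion symptoms (relative to baseline) on a 10-point visual scale".

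For the second objective (cardiopulmonary response) the same Data analyses section recognises that the test ends on symptoms or exertion. It adjusts for test time, either by keeping only the shortest duration or by expressing data as a percentage of total test time. The gait paragraph does not restate this. Its model sentence opens with the words *As above*.

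**The concern.** Gradient and time on test are the same axis, so the highest gradient at which a child supplies gait data is set by when that child stops. Stopping depends on exertion and symptoms. The Introduction also hypothesises that exercise will feel harder after concussion, and since a high RPE ends the test, the protocol's own expectation is shorter tests in that group. The children seen at high gradients are then a selected subset of those seen at low gradients, and the selection may differ between groups.

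A model that pools all minutes from all children reads a change in who is being measured as a change in gait with intensity. What is at stake is the group-by-intensity comparison in the third objective. The primary fMRI objective is not affected.

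**Working it through.** The documents give no gait figure to reproduce, so the check is by reasoning and simulation. From the documents: 40 children per group, gradient rising 1% per minute, and data kept to each child's own stop. Everything else is assumed.

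**Assumptions.** Gait variation for a child at minute t is level + slope x t + noise. Levels have a between-child SD of 1. Mean slopes are 0.10 (concussion) and 0.05 (control) per 1% gradient, so the true difference is 0.05. The slope SD is 0.04 and the residual SD 0.5. Stopping times average 11 min (concussion) and 15 min (control), with SD 3. Where stopping is selective, its correlation with the child's level or slope is 0.6 in absolute value.

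**Hand check of the mechanism.** Suppose patients with high gait variation stop early (correlation -0.6). The mean level of patients still walking at minute t is -0.6 x λ(z), where z = (t - 11)/3 and λ(z) = φ(z)/(1 - Φ(z)), ignoring rounding to whole minutes.
- Minute 5: z = -2, λ = 0.055, mean level -0.03 SD.
- Minute 14: z = 1, λ = 1.525, mean level -0.92 SD.
- The change in composition is about -0.88 SD over 9 minutes. The true rise is 0.10 x 9 = 0.90 SD. Between these two minutes the composition change almost cancels the real trend in patients.
- Still walking at minute 14: 1 - Φ(1) = 16% of patients, and 1 - Φ(-1/3) = 63% of controls.

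**Simulated group difference in slope** (true value 0.05 except in the last row; 300 replicates, 40 for the mixed model):

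| Who stops early | Pooled | Common window | Mean of per-child slopes | Mixed model, random intercept and slope |
|---|---|---|---|---|
| Stopping unrelated to gait | 0.050 | 0.048 | 0.050 | 0.050 |
| High-variation patients | -0.006 | 0.050 | 0.050 | 0.050 |
| Steep-slope patients | 0.020 | 0.049 | 0.048 | 0.046 |
| High-variation children, both groups | 0.031 | 0.048 | 0.050 | 0.050 |
| Same, mean stop 13 min in both groups | 0.049 | 0.049 | 0.049 | not run |
| High-variation controls | 0.088 | 0.053 | 0.051 | 0.050 |
| Low-variation patients | 0.106 | 0.048 | 0.049 | 0.047 |
| No true difference; high-variation children, both groups | -0.021 | 0.000 | 0.000 | not run |

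The SD of the estimate was 0.023 to 0.025 for the pooled fit, 0.034 to 0.045 for the common window (the shortest test in the sample), and 0.014 to 0.016 for per-child slopes.

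**Other settings.** With assumed mean stops of 15 min (control) and 10 min (concussion), and high-variation children stopping early in both groups, the pooled estimate was 0.038, 0.027 and 0.018 at correlations of -0.3, -0.5 and -0.7. It was 0.081 with selection in controls only, about -0.003 with selection in patients only, and 0.050 with equal stopping times. The within-child estimate was 0.049 to 0.051 throughout. In a milder case (mean stops 12 and 14 min, correlation -0.5) about 18% of the slope difference was lost.

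**Percent of test time.** Suppose both groups have the same true slope of 0.05 per 1% gradient and stopping is unrelated to gait. The rise over a whole test is about 0.05 x 11 = 0.55 in patients and 0.05 x 15 = 0.75 in controls, a spurious difference of about -0.20. The simulation gave -0.192. This scaling does not hold gradient constant.

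**The case against.** The strongest reply is that the article does not commit to the biased analysis. It says differences *may* be assessed by these models. Time in a Group x Time ANCOVA can be read as a within-child factor, and child-level terms are detail that a condensed article may leave to the full plan. *As above* may also carry over the test-time adjustment from the second objective, and its shortest-duration option would remove the selection. In addition, patients need medical clearance, and children whose gait or vestibular impairment precludes safe exercise are excluded, which removes some extreme cases. Controls stop on exertion too.

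Part of this stands. A missing random-effects statement would be no finding by itself, and the carry-over is a possible reading. But the article does fix the data window, the intensity axis and the model terms, and the window it gives for gait runs to test termination. *As above* most naturally refers to the models. If it does import the adjustment, neither option fits well: percent of test time does not answer a question about gradient, and the shortest duration discards the higher gradients and much of the precision.

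A reader might go further and infer that selective stopping must shrink the hypothesised steeper rise towards zero. The documents do not support that. They give no stopping times and no relation between stopping and gait, and the direction changes with who stops early. With no true difference, the pooled fit can be shifted below zero, which is not shrinkage at all. The steeper-rise comparison is itself partly inferred: the Introduction says variation increases with intensity, and the interaction enters through the Group x Time term.

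**Conclusion.** The concern holds in conditional form. As written, the gait trend is open to selective stopping, and it is unclear whether the cardiopulmonary adjustment applies to it. A pooled fit can bias the group-by-intensity effect downward if high-variation or steep-slope patients stop early, and upward under other patterns. There is no bias if stopping is unrelated to gait, and essentially none if stopping times and selection are alike in both groups. Against a true difference of 0.05, pooled estimates ranged from -0.006 to 0.106. All these sizes rest on the assumed stopping times and correlations. What does not depend on the direction is that within-child estimates stayed at 0.046 to 0.051, and per-child slopes had an SD roughly 60% of the pooled one (about 0.015 against 0.025). The point deserves a change to the plan, in proportion to a third objective.

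**What to change.** In the gait paragraph of Data analyses:

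1. Make the main analysis a within-child model of gait variation on gradient, for example a mixed model with a random intercept and slope per child, adjusted for age and sex, with group x gradient as the test.
2. State that percent-of-test-time scaling is not used for gait, so that the scope of *As above* is clear.
3. Add an analysis restricted to a common gradient range as a sensitivity analysis. It should not be the main comparison: it drops the gradients that the hypothesis targets and is not needed to remove the bias once slopes are within-child.
4. Tabulate the number of children contributing at each gradient, by group.

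The cost is a few sentences and slightly more modelling work, with no new data. The within-child model relies on a roughly linear trend within each child.
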